## Methods

### Theoretical Foundation of ET@home

The *Explore Transplant* (*ET*) education program was created based on Prochaska’s Transtheoretical Model of Behavioral Change (TTM) and research with over 1000 patients with CKD, to address gaps in their transplant knowledge [30]. *ET* allows transplant-eligible patients to explore the option of remaining on dialysis or pursuing DDKT or LDKT and make an informed choice after knowing their benefits and risks. The TTM holds that patients vary widely in their levels of readiness to make important decisions about their health [31], like whether or not to get an LDKT [32]. This study will employ educational resources from the *ET@Home* program that are based on the TTM and that are designed to help CKD patients at all stages of readiness and decision making around DDKT and LDKT learn more about their treatment options and to ultimately choose the option best for them. The *ET@Home* educational resources never pressure patients to pursue transplant of any kind; rather, they provide accurate information about the complex set of potential risks and benefits that need to be considered when deciding whether to get a DDKT or LDKT, including potential increases in length and quality of life, resuming life activities, implications of taking transplant medications, the chances of injury to a living donor, and many more factors.

### Study participants: Eligibility, recruitment, and randomization

KPSC provides coverage and care to nearly 65,000 patients with CKD Stages 3–5 throughout Los Angeles, San Diego, Kern, San Bernardino, Riverside, and Ventura Counties. About 24% of these patients are Hispanic, 52% White, 15% Black, and 9% Asian, similar to the broader CKD population in California. As of December 2015, more than 1500 KPSC CKD patients were listed on the United Network for Organ Sharing (UNOS) waiting list awaiting a DDKT, and approximately 700 additional KPSC patients were undergoing transplant evaluation. However, since 2014, only 350 KPSC patients have received a kidney transplant, with fewer than 100 patients receiving a LDKT.

Inclusion criteria for the study include adult KPSC patients between 18 and 70 years holding continuous membership with KPSC, currently being treated for CKD 3, 4, or 5/ESRD, having had at least one visit to a KPSC nephrologist in the last 18 months and who speak English or Spanish. To target enrollment of the CKD 3 patients at highest risk of worsening CKD, investigators will calculate a risk score for CKD 3 patients using the model described in Tangri et al. [33]

Exclusion criteria include having known medical or other permanent contraindications to transplant including cancer, heart failure, chronic obstructive pulmonary disease, hepatitis, cirrhosis, or dementia, or previous delisting or rejection for renal transplant by a transplant center. Other exclusion criteria include not being able to speak and read English or Spanish or having previously received a transplant. Those who have already refused to be evaluated for a transplant will also be excluded from the study. Patients’ transplant eligibility will be confirmed by reviewing relevant information (e.g., absence of serious heart disease or cancer) from their Kaiser electronic medical record.

Prospective participants who meet eligibility criteria will be sent an email inviting them to enroll in the study and asked to complete the initial transplant decision-making survey online or on the phone. Study staff will invite patients to participate in the RCT, beginning at the top of the risk-score ranked list, moving down the list until stratified cell targets are met. Recruitment will be stratified by race/ethnicity, language spoken, and CKD stage, oversampling smaller subgroups within the KPSC patient population. Expecting a response rate of 20%, an initial sample of 6000 patients will be invited to participate, resulting in a final sample of 1200 patients (Fig. 1). Clicking the survey link or contacting the study team by phone to begin the survey indicates consent to participate in the study. The email includes an opt out link if they do not wish to participate in the study. Invited prospective participants will receive follow-up invitations by secure email and phone to complete the initial transplant decision-making survey.

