#### Hypothesis

*Patients earlier in the CKD continuum, patients who speak Spanish, and non-White patients will have less knowledge about the opportunities for and risks and benefits of living kidney donation and will be making less informed LDKT decisions.*

### Aim 2

To conduct a randomized controlled trial in English and Spanish of *ET@Home* for CKD Stage 3–5 patients to assess its effectiveness to increase LDKT knowledge and decision-making by race/ethnicity and primary language spoken as compared to the standard KPSC education.

#### Hypothesis 1

*At the conclusion of the trial, CKD patients who receive ET@Home will have greater transplant knowledge and be more likely to make an informed treatment decision than patients receiving KPSC education alone.*

#### Hypothesis 2

*ET@Home will be more or equally effective for patients earlier in the CKD continuum, patients who speak Spanish, and non-White patients than patients in these subgroups receiving KPSC education alone.*

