### Evaluation and statistical analysis plan

#### Power analysis

Based on the following assumptions, we estimated the sample size for the RCT. Using data from previous RCTs [4, 35], a mean knowledge change score of 1.0 points is estimated necessary to be detected among patients receiving *ET@Home* and standard KPSC education. Patients’ baseline transplant knowledge scores will be correlated with those of other patients from the same clinics [intraclass correlation coefficient (ICC) of 0.31]. The variance in knowledge change has both between- and within-cluster components, yielding a pooled standard deviation estimate of 4.0. Participant retention will be 50% at the 6-month assessment. Outcomes will be assessed using two-tailed statistical tests. Type 1 error rate (alpha level) will be set at 0.05. This study design will ensure power of 0.90. Power calculations for this trial are based on all of these factors, which yields a standardized effect size, accounting for clustering of approximately 0.257.

Power analyses based on changes in transplant knowledge, our primary study outcome, are presented. The study design and analyses were treated as a test of the difference between the mean knowledge score change of CKD patients in the *ET@Home* and standard KPSC education (control) conditions six months post-baseline. It is estimated that with 600 completed surveys (50% attrition), there will be a 90% power to detect a 0.25 effect size between two equal-sized groups (control and treatment groups). By stratifying recruitment and randomization by race/ethnicity (Asian, Black, Hispanic, White), primary language spoken (English vs. Spanish), and stage of CKD, according to the table below, this sample size will also have 90% power to detect 1 point differences in change on the transplant knowledge scale between the *ET@Home* and standard KPSC education conditions for these critical subgroups using interaction terms (e.g., treatment by race interaction, language by race interaction). Patients enrolled and randomized are shown in Table 3.

**Table 3 Tab3:** Patients enrolled and randomized

Race/Ethnicity/Language	Stage of CKD			
	3^a^	4	5/ESRD	Total
*English-speaking Asian*	67	67	66	200
*English-speaking Black*	67	66	67	200
*English-speaking White*	67	67	67	200
*English-speaking Hispanic*	67	67	66	200
*Spanish-speaking Hispanic*	133	133	134	400
Total	400	400	400	1200

^a^
*CKD* 3 patient recruitment prioritized based on likelihood to progress

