### Statistical analysis

The available demographic and clinical characteristics of patients who refuse to join the study will be compared to those who enroll to determine if the patient selection procedure has resulted in a biased sample. A similar analysis will be conducted to compare the patients who fail to complete the six-month assessment. Multiple imputation by chained equations (MICE) will be used to multiply impute missing data. Imputation models will include all analysis and stratification variables. The intent-to-treat (ITT) approach will be applied in that all study participants will be analyzed according to the group that they were randomized to, regardless of whether they actually received their assigned intervention or not. Responses to the six-month intervention evaluation will be summarized for the sample overall and by levels of the stratification factors.

It is hypothesized that patients earlier in the CKD continuum, patients who speak Spanish, and non-White patients will have less knowledge about the opportunities for and risks and benefits of living kidney donation and will be making less-informed LDKT decisions. Investigators will evaluate these hypotheses using data from the pre-survey (baseline) by fitting multilevel random effects models with a random intercept to account for clustering at the CKD clinic level to compare differences in knowledge, informed decision-making, and Self-Efficacy. First, unadjusted models will be examined with the race/ethnicity, primary language spoken, and stage of CKD as independent variables for each test (separate models for each). Then, each of these models will be adjusted for other factors hypothesized to impact each outcome, including level of socioeconomic vulnerability, the level of previous transplant education received, the level of medical mistrust, and the level of health literacy. The addition of these variables will help test and control for confounding.

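### Filling CKD 3 race/language cells from the top of a risk ranking gives the cells different progression risk, which Aim 1's named adjusters do not remove

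*Protocol article*

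**What the plan says.** Under 'Study participants: Eligibility, recruitment, and randomization', the Protocol article says "investigators will calculate a risk score for CKD 3 patients using the model described in" a published source, so as to target those at highest risk of worsening. Staff then invite patients "beginning at the top of the risk-score ranked list, moving down the list until stratified cell targets are met". The footnote to Table 3 confirms that the ranking concerns CKD 3: "patient recruitment prioritized based on likelihood to progress".

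The cells are filled by design out of proportion to the source: "Recruitment will be stratified by race/ethnicity, language spoken, and CKD stage, oversampling smaller subgroups within the KPSC patient population". Table 3 sets CKD 3 targets of 67 for each of the English-speaking Asian, Black, White and Hispanic cells and 133 for Spanish-speaking Hispanic patients. On the source, the article says "KPSC provides coverage and care to nearly 65,000 patients with CKD Stages 3–5" and "About 24% of these patients are Hispanic, 52% White, 15% Black, and 9% Asian".

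Aim 1 compares baseline knowledge and decision-making by race/ethnicity and language over all of CKD 3–5. Its hypothesis is that "Patients earlier in the CKD continuum, patients who speak Spanish, and non-White patients will have less knowledge". 'Statistical analysis' fits race/ethnicity, language and stage in separate unadjusted models. It then adjusts each for other factors thought to affect the outcome, naming "level of socioeconomic vulnerability, the level of previous transplant education received, the level of medical mistrust, and the level of health literacy". Neither the risk score nor any measure of kidney function is named.

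**The concern.** Taking a fixed number from the top of a ranked list selects a thinner slice of a large group than of a small one. The White cell can be filled from the extreme top of the CKD 3 ranking. The smaller groups must be followed further down. Cells that are labelled with the same stage then differ in how close their members are to kidney failure, because of the invitation rule and not because of anything about the groups.

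Aim 1 is an observational comparison, so randomisation does not protect it. The article expects knowledge to be lower earlier in the disease. If that gradient also holds within CKD 3, part of an observed race or language difference in knowledge could come from the selection. Stage does not help as a stratifier or covariate: Table 3 already gives every race/language row about a third of its patients in each stage, and the imbalance sits inside CKD 3. The treatment-by-race and treatment-by-language interactions carry the same mix of risk, so an apparent difference in effect by language could partly be a difference in effect by risk.

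**Working it through.** **The plan's own figure.** 6000 invitations × 0.20 response = 1200 enrolled. This reproduces.

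**Invitations needed in CKD 3 at 20% response.** English-speaking cells: 67 ÷ 0.20 = 335 each. Spanish-speaking Hispanic cell: 133 ÷ 0.20 = 665.

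**Relative depth.** Depth in a cell = invitations ÷ (65,000 × eligible CKD 3 share × group share). Suppose the eligible CKD 3 share is equal across groups and Asian, Black and White patients are all counted as English-speaking. The eligible share then cancels:

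- Asian versus White: 0.52 ÷ 0.09 = 5.8 times deeper.
- Black versus White: 0.52 ÷ 0.15 = 3.5 times deeper.
- Spanish-speaking Hispanic versus White: (133 ÷ 67) × 0.52 ÷ (0.24 × s), where s is the share of Hispanic patients who speak Spanish. The article does not give s. The ratio is 17.2 for s = 25%, 8.6 for s = 50% and 5.7 for s = 75%.

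**From depth to mean risk.** Assume a standard normal score with the same distribution in every group. The mean of the top fraction p is φ(z_p)/p. The eligible CKD 3 share is not given, so 20%, 50% and 90% are tried. Each entry is the invited fraction, with mean risk in SD in brackets.

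| Cell | 20% eligible | 50% eligible | 90% eligible | White minus cell (SD) |
|---|---|---|---|---|
| White | 5.0% (2.07) | 2.0% (2.42) | 1.1% (2.63) | – |
| Black | 17.2% (1.48) | 6.9% (1.93) | 3.8% (2.17) | 0.46 to 0.59 |
| Asian | 28.6% (1.19) | 11.5% (1.69) | 6.4% (1.96) | 0.67 to 0.88 |
| Spanish-speaking, s = 25% | 85.3% (0.27) | 34.1% (1.08) | 18.9% (1.43) | 1.20 to 1.80 |
| Spanish-speaking, s = 50% | 42.6% (0.92) | 17.1% (1.49) | 9.5% (1.78) | 0.85 to 1.15 |
| Spanish-speaking, s = 75% | 28.4% (1.19) | 11.4% (1.69) | 6.3% (1.96) | 0.67 to 0.88 |

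The White versus Spanish-speaking gap is thus about 0.7 to 1.8 SD of risk.

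**From risk to knowledge.** Artefact within CKD 3, in SD of knowledge = risk gap × correlation r between risk score and knowledge in CKD 3. The article gives no r, so 0.1 to 0.3 is assumed.

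- Gaps of 0.4 to 1.0 SD: 0.4 × 0.1 = 0.04 up to 1.0 × 0.3 = 0.30.
- Pooled over three equal stages, of which only one is ranked, divide by 3: about 0.01 to 0.10.
- At the most extreme gap in the table (1.80 SD): 0.18 to 0.54 within CKD 3, and 0.06 to 0.18 pooled.

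**Scale.** A simple comparison of 200 with 200 at two-sided 0.05 and 80% power, ignoring clustering, detects 2.80 × √(2 ÷ 200) = 0.28 SD, where 2.80 is the sum of the normal quantiles 1.96 and 0.84. A pooled artefact of 0.01 to 0.10 SD is well below that, but it is a systematic shift that more patients would not reduce.

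**The case against.** A reader might infer that White CKD 3 patients will be closest to kidney failure and Spanish-speaking patients furthest from it, so that Aim 1 is biased towards its own hypothesis. The article does not establish this.

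- **Equal risk distributions are an assumption.** The Background says that Black and Hispanic patients have a higher chance of developing ESRD, which pushes the other way. The modelled White–Black gap is only about 0.5 to 0.6 SD, so a Black risk distribution higher by about that much would cancel it. Any upward shift in Hispanic risk shrinks the White versus Spanish-speaking gap. That passage offers no such offset for Asian patients. Equal risk in all five cells would still need a coincidence.
- **The order of the two Hispanic cells depends on s.** They reach equal depth at s = 133/200, about two-thirds. Above that, the English-speaking Hispanic cell goes deeper.
- **The race mix describes all 65,000 CKD 3–5 patients**, not eligible CKD 3 patients aged 18–70 with a recent nephrology visit. The latter mix is not given.
- **Aim 1 pools all stages.** No CKD 3-only contrast is stated, so the pooled figure is the relevant one for the planned analysis.
- **The hypothesised gradient runs along the CKD continuum.** That knowledge rises with the score inside CKD 3 is an extrapolation.
- **The adjuster list is open, and this is a condensed article.** A covariate it does not name is not a fault in itself, and adjusting for previous education might absorb part of the effect.

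These points limit direction and size. They leave the mechanism standing: the stated invitation rule, targets and source mix together create the imbalance, and the variable that drives the selection is the one to control.

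**Conclusion.** The point holds as a risk of confounding within CKD 3. From the article's own rule and figures, the risk cut-off will very likely differ by race and language, and nothing named in the analysis corrects for it. If risk distributions are similar across groups, the shift runs towards the Aim 1 hypothesis; higher ESRD risk in Black and Hispanic patients may offset part of it. The size is not determined by the article. The range of 0.04 to 0.30 SD of knowledge within CKD 3, or 0.01 to 0.10 SD pooled, rests on gaps of 0.4 to 1.0 SD and correlations of 0.1 to 0.3. The gaps themselves rest on assumed eligible and Spanish-speaking shares.

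The treatment-by-race and treatment-by-language interactions are touched to a lesser degree. It would be wrong to read this as a bias in the trial's main result: the arms are randomised within race/ethnicity, language and stage, so the overall comparison is unaffected. It is also no objection to enriching CKD 3 for progression, which is a stated aim. The point is that the degree of enrichment varies with the factors being compared.

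**What to change.** Keep the recruitment order and deal with the imbalance in the analysis:

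1. Add the risk score already calculated for CKD 3 patients to the Aim 1 race and language models, as a term nested within CKD 3 so that it applies only where the score exists.
2. Add the same term, with its interaction with treatment, to the treatment-by-race and treatment-by-language models.
3. Report the mean and range of the score in each CKD 3 race/language cell, and check the CKD 3 contrasts within the range of scores that the cells share.
4. State that CKD 3 results apply to higher-risk CKD 3 patients.

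The cost is one covariate that is already computed and slightly less precise group contrasts, since score and group will be correlated. Where the cells' scores barely overlap, adjustment relies on the model; step 3 would show this.

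A single cut-off for all cells, set by the one that goes deepest, is not advised. With 30% eligible and s = 30%, the deepest cell invites 665 / (65,000 × 0.30 × 0.24 × 0.30) = 47% of its pool. Applied everywhere, this lowers mean risk in the White cell from about 2.2 to 0.8 SD and largely undoes the intended enrichment.

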**Fig. 1 Fig1:**
[figure not shown]
Patient Recruitment Flowchart

After completing the initial survey, enrolled participants will be randomized in a 1:1 ratio, stratified by race/ethnicity, language spoken, and CKD stage, to either the *ET@Home* intervention condition or standard KPSC education. The randomization sequence is produced electronically within the data capture system. Once an enrolled participant is assigned to an intervention arm, the study team will send the participant a notification of their assignment. Since this is an educational intervention, neither the study participants nor the study team are blinded to treatment assignment.

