#### Outcome measures and research methodology

In order to verify and demonstrate impact on improving knowledge of the process, risks, advantages, and disadvantages of deceased and living donation among dialysis patients, an RCT will be conducted. In this RCT, 1200 CKD patients in the KPSC system will be randomized to one of two education conditions (patient-guided *ET@Home* vs. standard KPSC transplant education, 600 patients per condition). Changes in key outcomes will be assessed comparing patient data collected at baseline and six months post-baseline. The primary outcome measures include patients’ knowledge of CKD and the risks and benefits of transplant and the capacity to make an informed decision about transplant. Additionally, key secondary measures will be examined, including self-efficacy to pursue DDKT and LDKT and steps taken towards transplant.

Comparisons in the two educational conditions’ effectiveness will also occur for patients earlier in the CKD continuum, patients who speak Spanish, and non-White patients.

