#### Methodology

Patients will be remunerated $20 with a gift card after completing a baseline survey. Most surveys will be completed online by the study participants directly or over the phone with a trained interviewer. Any mailed surveys will be returned to KPSC and entered into the study’s assessment database. A double-data entry method will be used to ensure accurate data entry. Separate databases will be created for each patient’s registration/contact information and assessment data. Each patient will be given a unique, arbitrary study identification number that can be used to associate their contact and registration information and assessment data. Once the 1200 surveys have been collected and entered, this data will be analyzed to determine baseline differences in transplant knowledge, informed decision-making, self-efficacy, and steps toward transplant between patients varying in race/ethnicity, primary language, and CKD stage before patients are given an intervention.

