#### Process evaluation

At the six-month follow-up assessment, all intervention participants will complete an evaluation of the helpfulness of and their satisfaction with the print and video materials, text messages, and the *ET@Home* program as a whole.

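### The educational nature of the intervention explains open participants, but not why anyone asking the six-month outcome questions by phone should know the arm

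*Protocol article*

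**What the plan says.** The blinding statement closes the section on eligibility, recruitment and randomization: "neither the study participants nor the study team are blinded to treatment assignment". The reason given is that the intervention is educational. No other reason is given, and nowhere does the article exempt outcome interviewers. The same section has the study team notifying each participant of the assignment and places the randomization sequence inside the data capture system.

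On timing, that section states "After completing the initial survey, enrolled participants will be randomized in a 1:1 ratio". Under Outcome measures and research methodology, "Changes in key outcomes will be assessed comparing patient data collected at baseline and six months post-baseline".

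On what is measured, the same part says "The primary outcome measures include patients’ knowledge of CKD and the risks and benefits of transplant", together with the capacity to make an informed decision about transplant. Both come from the patient survey.

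On how the survey is taken, Methodology says "Most surveys will be completed online by the study participants directly or over the phone with a trained interviewer", and adds that "Any mailed surveys will be returned to KPSC and entered into the study’s assessment database". The share of surveys taken by phone is not given, for either time point.

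At the six-month assessment there is also a part for one arm only: under Process evaluation, "all intervention participants will complete an evaluation of the helpfulness of and their satisfaction with" the materials and the programme. Its position relative to the outcome items is not fixed.

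**The concern.** Blinding of participants and blinding of the people who collect outcomes are separate decisions. An education programme rules out the first. It has no bearing on the second, yet the article settles both in one sentence with one reason.

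The distinction matters because of the kind of outcome. An interviewer who knows that a participant received ET@Home can, without intending to, repeat a question, wait longer for an answer or probe a hesitant reply. Any of these could raise a knowledge or decision-making score in one arm. Intent-to-treat analysis and multiple imputation do not remove such a shift, and a larger sample only estimates it more precisely.

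**Working it through.** The article states no figure on this point, so the check is mainly a comparison of its sections.

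**Step 1: who is open to the arm?** The blinding sentence covers participants and the study team. No section separates interviewers from that team or describes any masking of outcome collection.

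**Step 2: does the reason support the choice?** That the intervention is educational means its recipient can see it. It does not follow that a person reading out questions six months later must know the allocation.

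**Step 3: can an interviewer reach the primary outcomes?** Yes, for some share of surveys. Online and mailed surveys are self-completed and involve no interviewer. Phone surveys do.

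**Step 4: when can the arm matter?** Randomization follows the baseline survey, so the baseline score cannot be affected. With change = six-month score − baseline score, as the Statistical analysis section defines it for knowledge, a shift at six months passes in full into the change score for that participant.

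**Step 5: how large could it be?** The article does not allow an answer. The following is an illustration only, on assumed values.

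Inputs from Power analysis: SD of knowledge change 4.0; 600 completed surveys, so 300 per arm; two-sided alpha 0.05; target difference 1.0 point. Assumptions: a share f of six-month surveys is by phone, and phone interviewing favours ET@Home by b points in that share.

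- Shift in the arm difference = f × b.
- Standard error = 4.0 × √(2/300) = 0.327, ignoring clustering by clinic and imputation.
- Rejection rate with no true effect = 1 − Φ(1.96 − shift/0.327) + Φ(−1.96 − shift/0.327).

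| f (assumed) | b (assumed) | Shift (points) | Two-sided error |
|---|---|---|---|
| 0.10 | 0.5 | 0.05 | 5.3% |
| 0.25 | 0.5 | 0.125 | 6.7% |
| 0.50 | 0.5 | 0.25 | 11.9% |
| 0.50 | 1.0 | 0.50 | 33.4% |

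The last row assumes that interviewers alone produce the whole 1.0-point target in every phone interview, which nothing in the article suggests. The table shows that the answer depends on two quantities the article does not give. It is not an estimate of the bias in this trial.

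**The case against.** The strongest reply is that the exposure is partly inferred. The sentence on survey mode follows the one on the baseline gift card, in a paragraph that ends with the baseline analysis, and the recruitment text mentions phone only for the initial survey. No sentence states the six-month mode on its own. The article also does not say whether the trained interviewer belongs to the study team or sees the allocation. Call-list displays and question order are details that a condensed article may leave to the full protocol.

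Part of this stands. The six-month phone share is unknown and could be small, so a reader should not infer that interviewers are shown to be biased or that most outcomes are exposed. What does not fall away is the stated choice. The article declares the team unblinded as a whole and gives a reason that does not reach outcome collection. That is text to correct, not detail left out.

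Three stronger readings are tempting and are not supported:

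- **Masking needs no extra staff.** The article gives no staffing information. Keeping contact and assessment data in separate databases does not show where the arm is visible; the sequence sits in the data capture system, and one identifier links the two databases. Staff who notify participants or send materials cannot be masked for those participants by hiding a field on a screen.
- **The programme evaluation will unmask the interviewer.** It would if asked before the outcome items, but no order is stated, and the Variables section mentions it after the outcome measures.
- **An analysis of self-completed surveys alone would settle the matter.** Survey mode is chosen after randomization and may differ by arm, so that subset no longer preserves the randomized comparison.

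It is also fair to say that participants know their arm and report the outcomes themselves. Masked interviewers do nothing about bias from that source.

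**Conclusion.** The point holds in a limited form. The stated reason justifies open participants; it does not justify arm-aware interviewers for the six-month primary outcomes. The route for bias is specific: phone interviews only, at six months only, directly into the change score. Its size cannot be stated, and no range in points should be read as evidence of it.

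The conclusion rests on two readings: that the sentence on survey mode applies at six months as well as at baseline, and that phone interviewers fall within the study team described as unblinded. If the full protocol shows otherwise on either, the remaining task is to correct the blinding sentence so that it says so.

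**What to change.** Amend the blinding sentence to say that participants and staff who deliver the intervention are unblinded, but that six-month phone interviews are done by interviewers, drawn from existing staff, who do not handle that participant's assignment or materials and whose call list and survey screen do not show the arm. Ask the ET@Home-only evaluation after all outcome items. Record survey mode and any unmasking for each six-month survey, and report both by arm.

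If an analysis limited to self-completed surveys is wanted, label it exploratory and state that it selects on a post-randomization variable.

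The cost is some separation of roles within the team, a display setting, a fixed question order and two recorded items. The sponsor has to confirm that the roles can be separated, since the article does not describe staffing. Masking will be partial because some participants will reveal their arm, which is why unmasking is recorded. The intervention, endpoints and sample size do not change.
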